### Methods in analysis to handle protocol non-adherence and any statistical methods to handle missing data {20c}

For the primary outcome, estimates of the effectiveness of the intervention under minimal and full compliance will be assessed using Complier-Average Causal Effect Analysis (CACE) [34]. The sensitivity of the primary analysis to the missing at random assumption will also be assessed.

### Plans to give access to the full protocol, participant-level data and statistical code {31c}

Reported here are the trial methods as set out in protocol version 2.9 20 May 2021. The full current protocol and previous versions showing protocol amendments to date are publicly available on the NIHR website: https://www.fundingawards.nihr.ac.uk/award/16/122/20.

Methods for the process, qualitative and economic evaluations are not reported here but are available in the full protocol.

Requests for other data or documentation should be made by contacting the corresponding author.

## Oversight and monitoring

### Composition of the coordinating centre and trial steering committee {5d}

The Trial Management Group (TMG) is the executive decision-making body and is responsible for overseeing the day-to-day running and management of the trial. The group comprises the Chief Investigator (CI and TMG Chair), Co-Investigators, Gateway Police Officers, Trial Manager, Qualitative & Process Evaluation Lead, Trial Statistician and Trial Coordinators. The TMG meets regularly with frequency according to the needs of the study. The CI has overall responsibility for the study. YTU is responsible for project management of the trial.

The SSC/DMEC, working to a study-specific Charter, provides overall supervision of the study on behalf of the sponsor and funders to ensure conduct is in accordance with the protocol. Membership of the SSC/DMEC comprises an independent Chair and three other independent members, a participant representative, the CI and the Senior Trial Statistician. Other study co-investigators may also attend the meeting at the invitation of the Chair. The committee meets at regular intervals and may request more frequent meetings when felt necessary.

The UoS is sponsor for this project and takes overall responsibility for the quality of study conduct.

### Composition of the data monitoring committee, its role and reporting structure {21a}

Due to the low-risk nature of the data in this study, the SSC will also take on the role normally undertaken separately by a data monitoring and ethics committee (DMEC). The independent members of the committee will be allowed to see unblinded data if required.

### Adverse event reporting and harms {22}

There are no anticipated adverse events or effects. The main risk for the participants is the nature of the topics discussed during outcome data collection interviews. These include discussions about their mental health, drug and substance use, and adverse childhood experiences. Offenders, who are allocated to receive the intervention, will also be encouraged to examine their own behaviour and its impact, which may be challenging and distressing for them. All assessments will be supported by the Navigators who are trained care workers experienced in dealing with this age group and discussing difficult issues.

The researchers and the care workers work closely and share experiences and concerns which can be raised at any of the relevant inter-disciplinary meetings.

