#### Content and delivery of Gateway intervention

##### Part 1: Initial assessment with a Navigator

Within 3–5 working days of their disposal, the Gateway Navigator will conduct a detailed needs assessment with the participant and mentor them through the programme. Based on the identified needs, the Navigator will connect the young adult with the appropriate services (e.g., alcohol, drugs, mental health and/or housing). The Gateway Navigators are trained support/case workers, provided by third sector organisation No Limits, and Southampton City Council. Assessments are held face to face whenever possible, but where necessary they are carried out via phone or video calls. Subsequent contacts are predominantly via telephone, text or video calling. Some additional face to face contact may take place based on risk factors and considering COVID-19 guidance and precautions. This would be in informal settings such as coffee shops or public outdoor locations.

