## Assignment of interventions: blinding

### Who will be blinded {17a}

Consent for eligibility screening, Gateway consideration, sharing of contact details and the randomisation is undertaken by the police investigators, none of whom are involved in data collection for the study.

UoS Research team members involved in obtaining Stage 2 consent and data collection will be blinded as far as possible to the randomised group. The CRFs include a tick box for the researcher to indicate whether they believe blinding was compromised during assessment, or other communications such as when booking appointments, and if so which of the allocation groups they believe the participant to be in.

The statistician will not be blinded to treatment allocation.

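### Navigator support for assessments, and unrestricted exchange between Navigators and researchers, threaten the blinding of the outcome interviewers

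*Protocol article*

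**What the plan says.** All references are to the protocol article.

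- **Adverse event reporting and harms {22}.** The paragraph opens: "The main risk for the participants is the nature of the topics discussed during outcome data collection interviews". It notes next that people allocated to Gateway may find the intervention distressing, and then says: "All assessments will be supported by the Navigators who are trained care workers experienced in dealing with this age group". The following paragraph states: "The researchers and the care workers work closely and share experiences and concerns which can be raised at any of the relevant inter-disciplinary meetings".
- **Who will be blinded {17a}.** "UoS Research team members involved in obtaining Stage 2 consent and data collection will be blinded as far as possible to the randomised group". As a record of failures, "The CRFs include a tick box for the researcher to indicate whether they believe blinding was compromised during assessment" or in other contacts, and which arm they suspect.
- **Plans for assessment and collection of outcomes {18a}.** The Southampton researchers read the questions aloud, may give guidance, and write down the answers. No Navigator is mentioned.
- **Part 1: Initial assessment with a Navigator.** "the Gateway Navigator will conduct a detailed needs assessment with the participant and mentor them through the programme". No Navigator role for control participants appears anywhere in the article.
- **Outcomes {12} and Participant timeline {13}.** WEMWBS is self-reported, by telephone interview, at 4 weeks, 16 weeks and 1 year. The 1-year value is primary. Gateway lasts 16 weeks from disposal.
- **Stage 1 consent.** Participants learn their allocation at disposal.

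**The concern.** Participants cannot be blinded here, so a blinded interviewer is the main remaining safeguard against differential questioning, prompting or recording. The harms section appears to place the staff who deliver the intervention alongside outcome collection, and it has the interviewers conferring with them without any stated limit. Navigators mentor only Gateway participants, so a Navigator's remark about a named person reveals that person's arm. If Navigators also support the interviews, a participant with a mentor in the background may answer differently from one without. Any resulting shift in WEMWBS would be read as an effect of Gateway.

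**Working it through.** The main check sets the passages side by side. Arithmetic serves only to show how sensitive the comparison is.

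**1. Which assessments does the harms section mean?**

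- *Outcome interviews:* these are the stated main risk in the same paragraph. The article also uses the word for outcome collection under the withdrawal heading in {11b}, in {17a}, and in {20a} for the three time points. Navigators conduct the Gateway needs assessment, so to say that they support it would be odd.
- *Gateway needs assessments:* the sentence directly before concerns the intervention, Part 1 uses the word for the Navigator's own work, and {18a} describes interviews held by researchers with no Navigator.

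The text does not settle this. Under the second reading, the paragraph offers no mitigation for the risk it calls the main one.

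**2. Which arm?** If outcome interviews are meant, there are two cases. Support for Gateway participants only makes interview conditions differ by arm. Support for everyone brings intervention staff into contact with controls. Neither is intended elsewhere in the article.

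**3. Does the exchange depend on that word?** No. The researchers are the interviewers (Stage 2 consent, {15}, {18a}), and the care workers in {22} are the Navigators. The statement "The researchers and the care workers work closely and share experiences and concerns" carries no restriction on discussing individuals. In addition, Navigators keep an engagement record in the shared system Huddle ({11c}), and the article does not say whether interviewers can see it.

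**4. Which time points?** Gateway ends at 16 weeks and {30} provides no post-trial care. Navigator involvement therefore bears directly on weeks 4 and 16, where WEMWBS is secondary. The 1-year interview is affected mainly if an interviewer still knows an allocation learned earlier.

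**5. Sensitivity of the comparison.** Inputs from {14}: difference 4, SD 10, two-sided 5%, power 90%, 20% attrition.

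- Plan's figure: n per arm = 2 × (1.960 + 1.282)² × 10² / 4² ≈ 131.4, so 132 (264 in total). The t-based version gives 132.3, so 133, and 266 in total as stated. Then 266 / 0.8 = 332.5, so 333, or 334 with equal arms. The plan's figures reproduce.
- SE of the difference = 10 × √(2/133) = 1.23 points.
- With no true effect and a differential reporting shift b, the chance of a significant result is P(|Z + b/SE| > 1.96):

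| Assumed shift b (points) | Chance of p < 0.05 |
|---|---|
| 0.5 | 6.9% |
| 1.0 | 12.9% |
| 1.5 | 23.1% |
| 2.0 | 37.1% |

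The shifts are assumptions, since the article gives none. The table describes any differential reporting from any cause. It does not estimate what the harms section would produce.

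**The case against.** **The stronger reading.** A reader might infer that the interviewers are unblinded, in the Gateway arm only, and that the two sections cannot both hold. The article does not support that.

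- Navigator involvement in outcome interviews is one reading of an ambiguous word. Support could also mean help for a distressed participant rather than presence.
- The one-arm claim is an inference from the Navigators' Gateway-only role. Taken literally, the sentence covers every participant.
- Blinding is promised only in qualified form ("will be blinded as far as possible to the randomised group"), and breaches are foreseen and recorded. Sharing experiences is not stated to include allocations.
- Navigator presence at the 12-month interview is doubtful, given the 16-week programme.

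**The size.** A reader might also take the 13% and 37% for shifts of 1 and 2 points as the cost of this defect. Participants who know their arm could produce such shifts even with perfectly blinded interviewers, so the figures cannot be attributed to this wording.

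**Other safeguards.** {12} cites response-bias testing of WEMWBS, {18a} has questions read as set out in the form, and police who randomise do not collect data. These help, but none stops an interviewer from learning the arm.

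**Detail left elsewhere.** The full protocol or SAP may hold working instructions or a sensitivity analysis. Their absence here is no fault. The point rests on what the article does state.

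What survives is the unreconciled wording and the open channel. An avoidable line to intervention staff is hard to square with blinding to the extent possible, and a tick box records a breach without preventing it.

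**Conclusion.** The point holds as a threat to interviewer blinding arising from statements that conflict, or at least sit badly together. The exchange between researchers and Navigators is a problem whatever is meant by assessments. Navigator support at interviews is a further problem only if outcome interviews are meant, and then under either reading of which arm is covered. Exposure is most direct at weeks 4 and 16, and indirect at 12 months through allocation already known. No unblinding is shown, and the direction and size of any bias are unknown. The conclusion assumes that Navigators have no control-arm role, which fits every description of them in the article, and that interviewers may discuss individual participants with them, which nothing in the article rules out.

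**What to change.** 1. Reword {22} so that Navigators support only Gateway needs assessments and workshops and have no role in the week 4, week 16 or 1-year interviews.
2. Make any distress-support arrangement for those interviews identical in both arms.
3. State that outcome interviewers neither discuss individual participants with Navigators nor see Navigator engagement records. Route concerns through an existing team member who does not interview.
4. Use the {17a} tick-box data for a sensitivity analysis of WEMWBS with and without interviews flagged as unblinded. Read it cautiously, because flagging may differ by arm and dropping flagged interviews could itself unbalance the comparison.

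The cost is protocol wording and a working instruction, with no new staff or data items. The downside is less direct contact between interviewers and Navigators. The change is still useful: the Trial status section reports 163 of 334 randomised, so 334 − 163 = 171 planned participants had yet to enter when the article was submitted.

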### Frequency and plans for auditing trial conduct {23}

The study monitoring plan, approved by the funder and sponsor, is reviewed regularly. The low-risk nature of this study and COVID-19 restrictions mean this study is largely monitored centrally by delegated team members. There are no plans to externally audit the study, but this will be facilitated if the sponsor wishes.

### Plans for communicating important protocol amendments to relevant parties (e.g. trial participants, ethical committees) {25}

All protocol amendments are agreed by the TMG, and where appropriate, the SSC/DMEC and Funders prior to submission for research ethics and sponsor approval. Amendments are documented in the protocol and once approved, a copy sent to the funders, SSC/DMEC and the sponsor. Important protocol modifications will be submitted to *Trials* as an amendment or update to this journal article.

Police investigators involved in recruitment will be notified of any relevant protocol modifications via their internal project website and the regular newsletter issued by HC.

### Dissemination plans {31a}

The study has the potential to create a wide impact by influencing and improving health and welfare, public policy and public services, and culture and society. To maximise impact of the study, we have developed a strategy that engages with our project partners and the wider public, in particular our PPI representatives and PPP. Use will be made of existing networks and social media to share lay summaries of the findings. In addition, presentations will be given to the College of Policing and other relevant organisations, agencies and events.

The primary academic output from the study will be the report to the NIHR PHR Programme. In addition, peer review publications and conference presentations will include academic public health, criminology and policing audiences.

Development of an impact strategy and project plan for engagement with policy makers is being undertaken by the Public Policy Research Facility at the UoS. The findings of the study will directly inform police decision makers at operational and strategic level across Hampshire and in other police forces. The study also has the potential to inform decisions at the level of the Crown Prosecution Service, Government legislators, where community outcomes like Gateway are part of the suite of mandated outcomes for offences.

## Discussion

The design of this novel study has evolved in response to real-world challenges requiring pragmatic adaptions. These have included revision of recruitment eligibility and increasing site participation; tailoring consent processes to accommodate the legal basis of police processes in line with UK GDPR regulations and changing the mode of contacting and engaging with our hard-to-reach study population.

In addition to living through the current pandemic, the changes in restrictions also impacted police practice. We have responded positively to each of these as appropriate, often with exploratory mitigating strategies. Barriers to participation will continue to be addressed, particularly for those participants in education, who work and/or with childcare commitments, are unemployed or are experiencing mental health difficulties. The above scenarios have been encountered in the pilot. Our PPI representatives have provided valuable advice in addressing many issues already and we will continue to seek their advice on mitigating barriers.

Lockdown measures prompted a change from initial face to face meetings with participants to engagement by telephone. Responses so far suggest a preference for over-the-phone interviews. Gathering of data with consent across both groups has not been done before using this methodology in this age group, with a non-recidivism primary endpoint.

The research processes have been successfully integrated with police usual processes. Challenges still arise; however, the increased level of communication and commitment by our co-production approach already demonstrates potential for future collaborations.

The pandemic has been a major driver for the current design of this pragmatic trial and the recruitment and retention strategies adopted. These have enabled recruitment and data collection during lockdowns and social distancing, future proofing for the duration of the remaining recruitment period during continued uncertain times.

Multi-agency collaboration remains at the heart of the Gateway programme and delivery of this RCT. This unique study is expected to contribute robust evidence to allow local and national Police Commissioners to evaluate the possible benefits not just in the primary outcome of mental health, but on recidivism. The results will be used to inform policy decisions and best practice for similar interventions across the UK.

## Trial status

The current UoS REC-approved version of the protocol is version 2.9, 20 May 2021. This manuscript is a restructured and edited version of the current protocol to comply with the SPIRIT guidelines. Recruitment into the Gateway trial commenced in 1 October 2019 and the internal pilot phase was successfully completed. National restrictions in response to the COVID-19 pandemic resulted in the temporary suspension of recruitment from 22 March 2020 to 4 September 2020. Recruitment is ongoing at the time of manuscript submission, and to date, 163/334 participants have been randomised (2021). As a result of delays in study setup and lower than anticipated recruitment rates, a request for a funded extension has been submitted to NIHR PHR with an anticipated recruitment completion date of September 2023.

## Abbreviations

ACE: Adverse Childhood Experiences questionnaire
ADIS: Adolescent Drug Involvement Scale
AUDIT: Alcohol Use Disorders Identification Test
BRFSS: Behavioural Risk Factor Surveillance System
CARA: Conditional Cautioning and Relationship Abuse
CI: Chief Investigator
CPS: Crown Prosecution Services
CRF: Case Report Form
CSRI: Client Service Receipt Inventory
DMEC: Data Monitoring and Ethics Committee
HC: Hampshire Constabulary
HMPPS: Her Majesty Prison and Probation Services
HRA: Health Research Authority
HYOT: Hampshire Youth Offenders Team
IoW: Isle of Wight
NHS: National Health Service
NOMS: National Offender Management Services
OCBI: Out-of-court community-based intervention
OR: Odds ratio
PI: Principal Investigator
PIS: Participant Information Sheet
PNC: Police National Computer
PPI: Patient and Public Involvement
PPP: Public Participation Panel
REC: Research Ethics Committee
RCT: Randomised controlled trial
RJ: Restorative justice
RMS: Record Management System
SF-12: Short Form 12 questionnaire
SSC: Study Steering Committee
TMG: Trial Management Group
UoS: University of Southampton
UoY: University of York
WEMWBS: Warwick-Edinburgh Mental Well-being Scale
YTU: York Trials Unit
